### Recruitment strategy

Flyers are sent out to multiplicators. Recruitment in online forums is conducted. Patients contacting the study sites and cooperating institutions will be informed about the study and screened for eligibility if they are interested in participating. The expected completion date of the recruitment period is January 31 st, 2026.

## Interventions

### MBT

Patients in MBT will receive a maximum of 58 sessions in total. Of those, 30 are weekly individual sessions. 28 sessions are weekly group sessions conducted by two therapists, and consisting of 8 introductory sessions of group psychoeducation (MBT-I) followed by 20 group therapy sessions. The duration of MBT is 12 months. The therapists, who must be specialized in PT and at least be in advanced psychotherapeutic training, will receive a 3-day training in MBT as well as an online course and supervision. MBT is manualized and relies on validating the emotional experience of patients that aims to promote mentalizing. The proposed mechanism of change in MBT is to stabilize mentalizing in certain focus areas in order to create a psychic buffer between affect and behaviour to foster affect regulation, reduce impulsivity and promote functional, supportive relationships.

### BFT

Patients in the control arm will receive CBT or PT which are standard psychological psychotherapies in Germany paid for by the health insurances. CBT and PT are “bona fide treatments” (BFT) in Germany. Patients in BFT can choose whether they want to receive CBT or PT and will receive one to two weekly sessions conducted by community experts delivered as short-term psychotherapy (≤ 24 sessions) or long-term psychotherapy (> 24 sessions). Under some circumstances, patients can change their therapist. BFT can be delivered as individual, group or a combination of individual and group treatment as stated in the German Psychotherapy Regulations. CBT can be delivered with up to 80 sessions. The therapists delivering CBT or PT in the control group should at least be in advanced therapeutic training and can´t be certified practitioners in DBT, MBT, schema-focused or transference-focused therapy. CBT is defined as an approach that relies on learning and social psychology, requires an analysis of etiological and maintaining causes of the mental disorder (behavioural analysis) and uses techniques such as operant conditioning, cognitive restructuring and learning new forms of self-control. PT according to the German Psychotherapy Regulations can be delivered with up to 100 sessions. PT is defined as an etiological approach that focuses on unconscious psychodynamics and currently active (neurotic) conflicts as well as problems in functioning. PT therapists use clarification, confrontation and interpretation as core techniques and address phenomena of transference, countertransference and resistance to engage the patient in the therapeutic process and explore topics, emotions, and interpersonal patterns that patients would typically avoid dealing with. Elements of BPDspecific therapies are allowed in BFT; however, BFT should not represent regular MBT, DBT, schema therapy or transference-focused treatment practiced by certified practitioners.

## Additional treatments

Additional treatments except concomitant psychotherapy (including inpatient psychotherapy > 4 weeks) will be allowed in the two arms of the trial. Additional treatment can comprise pharmacotherapy, rescue medication, self-help groups, managed care, crisis interventions in psychiatry. Most trials in BPD so far have allowed concurrent psychotropic treatments [25] which reflects the use of pharmacotherapy in BPD [46]. All additional treatments will be systematically assessed and controlled for in data analysis. Changes in psychotropic treatment are measured as a secondary outcome.

## Procedure

### For an overview of assessments, schedule of enrolment and interventions see Table 1.

Diagnostic assessments to ensure inclusion/exclusion criteria will be carried out by trained clinicians using the Clinical Version of the Structured Clinical Interview for DSM- 5 [47] and the BPD and schizotypal personality part of the IPDE [44]. Raven’s progressive matrices (RPM- 2 [45]) will be used to assess IQ in case the clinicians suspect intellectual disability. Diagnostic assessments will be videotaped and 10% will be selected to be rated by all raters for reliability testing.

**Table 1 Tab1:**
[figure not shown]
*S*chedule of enrolment, interventions, and assessments

^a^EMA: every second day, one week per month in the first year and one week every three months in the second year

^b^after each therapy session and at t_1_ and t_2_

Data will be gathered and managed via redcap by the data coordinator (SHa) of the PI’s (ST) study site. Clinical monitoring will be conducted by the independent clinical monitor KKS to ensure patient safety, protocol adherence, and data consistency. For important protocol modifications, approval of the ethics committee will be obtained and the protocol published on the clinicaltrials.gov website will be updated.

Treatment duration in BFT is delivered as usual (according to the German Psychotherapy-Guidelines “Richtlinienpsychotherapie”). Thus, it can be shorter or longer than MBT (12 to 100 h); however, the average number of BFT treatment is comparable with 48 sessions per patient [48]. The length of BFT will not be controlled for by the study to ensure BFT conditions as in the German routine health care. Exact treatment length and dose will be assessed. To avoid the effects of attention bias, supervision will be regularly offered to therapists in both arms in their respective methods in a group setting. All interventions are implemented as face-to-face interventions. Individual and group therapists can be the same or different therapists. All therapies in the trial will be paid for by the German health insurances.

All therapy sessions will be video-recorded or, if video is not possible, audio-taped. Ten percent of random sample recordings from early and late phases of therapy across the whole recruitment phase will be analysed by external coders for therapist adherence. Trial results will be communicated by publication in journal articles and by congress participation.

## Instruments

### Eligibility screen

#### International personality disorder examination – borderline and Schizotypal personality disorder sections

The International Personality Disorder Examination (IPDE; [44], German version by [49]) is a clinical interview that follows a semi-structured format, utilized to assess personality disorders according to the classification systems outlined in the ICD- 10 and DSM-IV. For this study, the 15 items regarding BPD, as outlined in the DSM-IV, which are answered on three-point Likert scales (0 = “absent”; 2 = “pathological or meets criterion”) will be used. A time criterion will be added to identify whether the suicidal behaviour and self-harm occurred in the last 24 months and at least one in the last six months. In addition, the IPDE will be used to diagnose schizotypal personality disorder (9 items), as this is an exclusion criterion. The interrater-reliability for BPD diagnosis according to ICD- 10 is between *k* = 0.76 and *k* = 0.78 with a temporal stability of *k* = 0.62 to *k* = 0.65 [50].

#### Structured clinical interview for DSM- 5 – clinical Version

Major mental disorders will be assessed with the German version of the Clinical Version of the Structured Clinical Interview for DSM- 5 disorders (SCID- 5-CV; [47]). The SCID- 5-CV is the latest version of a well-established interview used to assess major mental disorders. The criteria are rated either as yes, fulfilled (or “ + ”), or no, not fulfilled (or “- “).The diagnostic sensitivity/specificity are above 0.70, the kappa coefficient values have been shown to be *k* > 0.70 for almost all diagnoses [51].

#### Raven’s progressive matrices 2, clinical edition

The Raven’s progressive matrices (RPM- 2; [45]) evaluate general cognitive ability, also known as *eductive* or meaning-making ability. In this study, the paper–pencil version of the Standard Progressive Matrices (SPM) will be employed in case of suspected mental retardation. The SPM include five sets of items that show a sequence of incomplete geometrical designs with increasing difficulty. Test-takers are required to identify the correct component to fill in the missing part of the designs from a list of given options. The items in each set follow a different logic, with the sets themselves becoming progressively more challenging. The reliability of the instrument is *r* = 0.75 and *r* = 0.93, depending on the age group [45].

#### Sociodemographics

Age, gender and a proxy for crystalline intelligence will be assessed as sociodemographic variables during the appointment for recruitment and confirmation of eligibility for the patients. To approximate the assessment of crystalline intelligence, the Berlin Test for the Assessment of Fluid and Crystallized Intelligence—Short Form Crystallized Intelligence (BEFKI GC-K) will be used. The BEFKI GC-K [52] is a measure for screening declarative knowledge via 12 questions with four response options each and an overall task duration of 5 min. Reliability of the 12-item scale is *α* = 0.70.

### Primary outcome

#### Crisis events – composite outcome

The primary outcome of the study is the incidence of crisis events as indicated by 1) suicides, 2) suicide attempts, or 3) self-harm behavior.

To assess suicide attempts and self-harm behavior, the following four questions taken from the Self-Harm Behaviour Questionnaire ([53], German version: [54]) will be used: “Have you ever intentionally hurt yourself or caused yourself pain? (e.g. scratched with fingernails or with other sharp objects?)”, “How often have you intentionally hurt or caused yourself pain?”, “Have you ever tried to take your own life?” and “How often did you try to take your own life?”. These questions will be adapted for the Ecological Momentary Assessment (e.g., “Since the last signal have you ever intentionally hurt or caused yourself pain? (e.g., scratched with fingernails or with other sharp objects?”). Only if any of the crisis events occurred, the patient will be asked to indicate the frequency of the event(s).

Crisis events like suicides cannot be reported by the patient themselves but should be taken into account as well (see e.g. Bateman and Fonagy [18]). Suicides are recorded via the Serious Adverse Events (SAE) reports.

To increase ecological validity, the incidence of crisis events 1) – 4) will be assessed during one week each month over the course of 12 months of treatment, and one week every three months post treatment up to the 12-month-follow up (T3). During the assessment week, patients will be asked to complete one online-assessment every other day, resulting in 4 assessments per assessment week.

### Secondary outcomes

#### Crisis events—individually

To gain deeper insights, the incidences of 1) suicides, 2) suicide attempts, and 3) self-harm behavior will be analyzed individually.

#### International personality disorder examination – borderline personality disorder section

In addition to its use for eligibility screening, the IPDE BPD section [49] will be used as a secondary outcome to assess changes in BPD diagnosis.

#### Borderline symptom list – short version

The Borderline Symptom List – Short Version (BSL- 23; [55]) will be used to assess borderline-specific clinical symptoms in the last seven days, i.e., the degree of severity. The items are answered on a 5-point Likert scale ranging from 0 = “not at all” to 4 = “very strong”. The degree of severity is calculated as a mean of the valid items. The internal consistency of the instrument is excellent (*α* = 0.94–0.97) [55].

#### Depression, anxiety and stress scale – 21 items

The self-report Depression, Anxiety and Stress Scale – 21 Items (DASS- 21; [56], German version: [57]) will be used to assess emotional states of depression, anxiety and stress in the last seven days. Each of the three scales consists of seven items which are answered on a 4-point Likert scale (0 = “did not apply to me at all”; 3 = “applied to me very much or most of the time”). The score for each scale is quantified by adding up the scores of the items. The reliability of the scales is between *α* = 0.78 and *α* = 0.91 [57].

#### World health organization disability assessment schedule 2.0 short form

The World Health Organization Disability Assessment Schedule 2.0 Short Form (WHODAS 2.0 short; [58]) is a self-report tool for evaluating health and disability in the last 30 days that covers the following domains of functioning: cognition, mobility, self-care, getting along with others, life activities and participation in community activities. The 12 items are answered on a 5-point Likert scale (1 = “none”; 5 = “extreme”). A total score is obtained as a sum of all items. The reliability of the scale tested in a sample of outpatients with psychotic disorders is good (*α* = 0.89) [59] and has showed a good to excellent internal consistency in a sample of patients with anxiety and stress disorders [60].

#### EQ- 5D- 5L

The EQ- 5D- 5L [61, 62] is a self-report, generic questionnaire that contains two parts: a five-item descriptive system and a visual analogue scale resembling a thermometer, with a range of 0 to 100. It measures five dimensions: mobility, self-care, usual activities, pain/discomfort, and anxiety/depression. Respondents can choose from five options: level 1 (no problems), level 2 (slight problems), level 3 (moderate problems), level 4 (severe problems), and level 5 (extreme problems or'unable to'). The ratings are added up to create a health profile. The reliability of the scale in patients with depression has been shown to be *α* = 0.77 [63].

#### Adult service use schedule

The Adult Service Use Schedule (AD-SUS; [64]) will be adapted for BPD and used to assess employment status, gross pay per year as well as hospital services, other BPD-associated services and community services used, use and dosage of (psychotropic) medication and indirect costs associated with BPD. The questions refer to the last 6 months. The original AD-SUS instrument is used as an interview, but for this study it will be adapted to a self-report questionnaire.

#### Dissociation-Tension scale- 4

The Dissociation-Tension Scale- 4 (DSS- 4, [65]) is a four-item self-report questionnaire used to assess acute dissociative symptoms. The items are answered on a 10-point Likert scale (0 = “not present” to 9 = “very strong”). The total dissociation score is calculated by forming the mean of the four items. The internal consistency of the scale is good (*α* = 0.87) [65].

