To investigate efficacy of MBT versus BFT, a total of *n* = 544 patients with a BPD diagnosis will be screened for eligibility at five study sites in Germany: University Hospital Heidelberg (Institute for Psychosocial Prevention, ST, and Department of General Psychiatry, SHe), University Hospital Jena (Institute for Psychosocial Medicine, Psychotherapy and Psychooncology, BS), University Hospital Düsseldorf (Clinic for Psychosomatic Medicine and Psychotherapy, UDE & JR), University Hospital Ulm (Clinic for Psychosomatic Medicine and Psychotherapy, HG, JV), Psychologische Hochschule Berlin (Department of Clinical Psychology and Psychotherapy, TS). Of the patients screened, *n* = 304 are expected to fulfil all inclusion criteria including informed consent to participate in the trial, to complete the baseline assessment (T0) and to be allocated to the trial (Fig. 1). Patients will be randomized in groups of 8 (randomization cluster) in a 1:1 ratio to either MBT or BFT using block randomization. Randomization will be stratified by study site. For randomization, study site coordinators will use a centralized web-based tool (randomizer.at) to maintain allocation concealment. Role-based user rights ensure that only approved study personnel may perform randomizations. Main assessments will be conducted for both arms at 6 months (in-therapy assessment, T1), at 12 months (T2) and at 24 months after start of therapy (12-months follow-up, T3). A final sample of *n* = 304 is expected to be obtained for data clearance and analysis using an intent-to-treat protocol. A drop-out of 30% during therapy is expected and acknowledged in our power analysis. Blinding of study team, trial personnel at site as well as patients is not feasible due to the nature of the interventions. Only central assessors will be blind to treatment. Allegiance bias is minimized as the consortium includes representatives of all trial treatments (MBT, group therapy, BFT).

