### Cost-effectiveness analysis

A within-trial cost-effectiveness analysis (CEA) will be conducted from a societal perspective. We assess the health-related quality of life using EQ- 5D- 5L [61, 62] to calculate the quality-adjusted life-years (QALYs). The patients will be asked to complete the EQ- 5D- 5L questionnaire at baseline (T0), in-therapy assessment (T1), post-therapy assessment (T2), and follow-up assessment timepoint (T3). The estimated costs for the two treatment groups are composed of direct medical, direct non-medical, and indirect costs. The direct medical costs include the intervention costs and BPD-associated medical costs, which will be calculated by multiplying resources by their corresponding unit costs. Data on the use of health and social services will be collected via a modified version of the Adult Service User Schedule (AD-SUS) adapted for use in the BPD patients through self-report [116]. The baseline AD-SUS will cover the period of 6 months prior. At the T1, T2 and T3 follow-up assessments, the AD-SUS will cover the period since the last assessment. The unit costs will be collected from regularly published sources and will be updated on a yearly basis as there is no obligatory unit cost list in Germany [117, 118]. The intervention costs of MBT or BFT, in contrast, will be collected using the records from the RCT, including activities, facilities, and overhead costs. We also include the costs of MBT or BFT by project staff spent with the patients on the telephone or in person, clinical training, supervision, and materials. Indirect costs will be analyzed using the Human Capital Approach, which measures the productivity losses as a result of time off work due to absenteeism or reduced productivity at work due to work disability.

Both costs and QALYs are discounted at 3% per year. Each treatment modality will calculate the incremental cost-effectiveness ratio (ICER) separately. Then we will perform an incremental analysis to select a cost-effective intervention strategy. Sensitivity analyses will be conducted to assess the robustness of the results depending on protocol deviations.

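### The protocol gives the AD-SUS two recall periods that conflict at T3; if the 6-month wording is used, months 12–18 go unrecorded

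*Protocol article*

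**What the plan says.** Three places in the protocol article bear on this.

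- *Adult service use schedule* (under Secondary outcomes) describes the version adapted for this trial as a self-report questionnaire. It covers employment and pay, hospital and community services, and "use and dosage of (psychotropic) medication and indirect costs associated with BPD". On the recall period it says only "The questions refer to the last 6 months", for no particular visit.
- *Cost-effectiveness analysis* makes the AD-SUS the source of service-use data: "Data on the use of health and social services will be collected via a modified version of the Adult Service User Schedule (AD-SUS"). It sets recall by visit. For T0, "The baseline AD-SUS will cover the period of 6 months prior". For the rest, "At the T1, T2 and T3 follow-up assessments, the AD-SUS will cover the period since the last assessment". Intervention costs are handled separately, from the trial's own records.
- *Aim, design and setting* places the main assessments "at 6 months (in-therapy assessment, T1), at 12 months (T2) and at 24 months after start of therapy (12-months follow-up, T3").

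The analysis these data feed is stated as follows: "A within-trial cost-effectiveness analysis (CEA) will be conducted from a societal perspective". QALYs come from the EQ-5D-5L at T0, T1, T2 and T3.

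**The concern.** The visits are not evenly spaced. A fixed 6-month look-back fits the first two follow-up visits but not the third, which comes 12 months after the one before. The two recall rules therefore cannot both hold at T3, and the article does not say which one the questionnaire uses.

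Cost-effectiveness is a named secondary objective, taken from a societal perspective. The Background section says hospital stays are the main driver of direct costs in this disorder and productivity losses due to disability the main driver of indirect costs. The AD-SUS is meant to capture both. If half of the follow-up year were not asked about, the AD-SUS part of each patient's cost total would cover less time than the QALYs it is set against. A period that was never asked about at T3 cannot be recovered reliably afterwards.

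**Working it through.** The plan states no figure to reproduce. The check is interval arithmetic on the stated visit times.

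**Inputs**

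- Visit times from *Aim, design and setting*: T1 = 6, T2 = 12, T3 = 24 months after start of therapy. T0 is taken as month 0 (an assumption, see the end of this field).
- Rule A, from *Adult service use schedule*: recall of 6 months at every visit.
- Rule B, from *Cost-effectiveness analysis*: 6 months before T0, then the time since the previous assessment.

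**Formulas**

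Gap = time of this visit − time of the previous visit.

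Uncovered time = max(0, gap − recall period).

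**Results**

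| Visit | Gap (months) | Rule A recall | Rule A covers | Rule A uncovered | Rule B recall | Rule B uncovered |
|---|---|---|---|---|---|---|
| T1 | 6 − 0 = 6 | 6 | 0–6 | 0 | 6 | 0 |
| T2 | 12 − 6 = 6 | 6 | 6–12 | 0 | 6 | 0 |
| T3 | 24 − 12 = 12 | 6 | 18–24 | 12 − 6 = 6 | 12 | 0 |

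- Rule A: 6 + 6 + 6 = 18 of 24 months covered. Months 12–18 are missing: 6/24 = 25% of the horizon and 6/12 = 50% of the follow-up year.
- Rule B: 6 + 6 + 12 = 24 of 24 months covered.

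The rules agree at T0, T1 and T2 and differ only at T3. The cost-effectiveness section names no AD-SUS collection between T2 and T3 that would close the gap under Rule A.

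**Consequence for the ICER under Rule A**

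Write each arm's mean cost as I + A, where I is the intervention cost (trial records) and A the AD-SUS-based cost. I is complete under either rule. A lacks the amount incurred in months 12–18, so the cost total is too low in both arms. The incremental cost is wrong by the between-arm difference in that missing amount, and the ICER by that difference divided by the QALY difference. The documents give no cost figures, so neither the size nor the sign can be calculated. The error would be zero only if the arms had equal AD-SUS costs in that half-year.

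**Assumption on T0**

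T1 is timed from start of therapy, not from T0. If patients wait w months between T0 and therapy, the gap from T0 to T1 is 6 + w, and Rule A would also leave w months uncovered at T1. The article does not state w. The table uses w = 0.

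**The case against.** The best defence is that the cost-effectiveness section already settles the matter. It is the section that governs cost data, it separates baseline from follow-up deliberately, and its rule leaves nothing uncovered. The instrument description is one general sentence that happens to be right at three of the four timepoints. A careful reader would let the specific rule prevail. This stands as the likelier intention, and it means that no loss of data has been shown. It does not remove the conflict. The 6-month sentence sits in the description of the trial's adapted questionnaire, directly before the article contrasts that version with the original interview, so it is not easily read as describing only the source instrument. A form built from that description would carry the wrong window at T3.

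A reader might also draw three stronger conclusions that the documents do not support.

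- *That a quarter of the cost data will be lost.* This is true only if the T3 form follows the 6-month sentence. Nothing in the article shows that it does. Even then, only AD-SUS items are affected, and employment status and annual gross pay do not naturally depend on the look-back. Time-based items do.
- *That the gap favours one arm because BFT may continue after month 12 while MBT has ended.* The cost-effectiveness section takes the intervention costs of both arms from trial records, and *Procedure* says that exact treatment length and dose will be assessed. BFT sessions in months 12–18 are therefore captured whatever the AD-SUS asks. No documented mechanism for a loss in one arm only remains.
- *That an additional AD-SUS at month 18 is needed.* That would be new data collection to shorten recall. Whether 12 months is too long for self-report is a fair question, but a separate one. The contradiction can be resolved without it.

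**Conclusion.** The inconsistency is real and confined to T3 if T0 is close to start of therapy: the article prescribes both a 6-month and a 12-month recall for the same form. Its effect is conditional. Under the 6-month wording, AD-SUS-collected service use, medication and time-based indirect costs for months 12–18 are missing (6 of 24 months, half of the follow-up year), and a cost total covering 18 months for these items is set against QALYs covering 24. Under the cost-effectiveness wording, nothing is missing. Intervention costs are complete in both cases.

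The conclusion rests on the stated visit times and on there being no AD-SUS collection between T2 and T3. Table 1 is not available, but the cost-effectiveness section lists only T1, T2 and T3 as follow-up AD-SUS visits. The point touches a secondary, health-economic analysis. The primary outcome, from ecological momentary assessment and serious adverse event reports, is not affected. It should be corrected, because a wrong form at T3 would do damage that the analysis could not repair.

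**What to change.** Amend the recall sentence in *Adult service use schedule* so that it matches *Cost-effectiveness analysis*, with one recall period per timepoint:

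- T0: the preceding 6 months.
- T1 and T2: the period since the last assessment.
- T3: the 12 months since T2.

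Then check that the T3 questionnaire in the data-capture system is worded this way, and correct it if it is not.

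The cost is a change of wording and one check of the form. The drawback is a 12-month self-report recall at T3, twice the nominal 6 months at the other visits. The cost-effectiveness section already implies this, so the fix adds no burden beyond the existing plan.
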